### 8.3. Number of subjects

- Test group (MegaShield group) : 70 patients
- Control group (Guardix-SG group) : 70 patients
- Total number of subjects : 140 patients

### 8.4. Basis for calculation

Suppose that the esophageal movement score (Marshmallow esophagography score) of the test group (MegaShield) is not lower than that of the control group (Guardix-SG) after thyroidectomy (non-inferiority test). In other words, this study is to test whether the test group is non-inferior to the control group. The null hypothesis is that the test group is not non-inferior in the mean of parameters to the control group, and the alternative hypothesis is that the test group is non-inferior in the mean of parameters to the control group [17].

Null hypothesis  $H_0$  :  $\varepsilon \leq -\delta$  , and

alternative hypothesis  $H_a$  :  $\varepsilon > -\delta$ .

$$n_1 = \frac{2(z_{\alpha/2} + z_{\beta})^2 \sigma^2}{(\varepsilon - \delta)^2}$$

where,  $\alpha$  : significant level     $1 - \beta$  : power,  $\sigma^2$  : variation,

$\varepsilon$  = difference between the means of the esophageal movement scores of the two anti-adhesion products (test group - control group), assuming there is no difference between the two groups ( $\varepsilon=0$ ),

$\delta$  = margin (limits of non-inferiority), 0.1 (the degree to which is regarded to be clinically significant)

To take into account both the existing comparator and placebo effect when setting the limits of non-inferiority, assume that:

'The effectiveness of the new treatment is non-inferior to that of the existing one' and 'the effectiveness of the new treatment is superior to the placebo effect.'

The margin that satisfies the above assumptions is obtained by the following expression:

$$\Delta = \frac{r}{1+r}(\theta_A - \theta_P)$$

For  $r$ , the difference between the active control and placebo is not used as the margin, and  $[0, 1]$  median is given to consider that  $r$  is smaller than the difference. The margin is multiplied by the ratio of  $[0, 1/2]$  to the difference between the historical active control and placebo.

In the previous study [16], the difference in scores between comparator (Guardix) and Placebo is  $2.93 - 2.73 = 0.2$ , so assuming that  $r$  is 1, the margin is  $0.2/2 = 0.1$ .

Assuming that:

$\alpha$  (Significance level) is 5%,

$\beta$  (power 80%) is 0.2,

$\delta$  (margin) is 0.1, and

$\sigma$  (variation) is 0.2,

the sample size is:

$$n_1 = \frac{2(z_{\alpha/2} + z_{\beta})^2 \sigma^2}{(\varepsilon - \delta)^2} = \frac{2(1.96 + 0.84)^2 0.2^2}{(0 - 0.1)^2} = 62.8.$$

Therefore, 63 subjects are calculated per group, and considering 10% drop-out, 70 subjects per group, that is, a total of 140 subjects, are required.

## 8.5 Subject recruitment plan

If necessary, subjects can be recruited by posting a public notice of recruitment on the bulletin board in the hospital.

## 9. Study period

32 months from the date of approval of IND by the Ministry of Food and Drug Safety

- Review period by the IRB : 3 months
- Subject recruitment period : 21 months
- Observation period for efficacy : 3 months
- Statistics processing period : 3 months
- Period for creating study report : 2 months
- 

## 10. Procedure (usage, method of use, period of use, combination therapy, etc.)

### 10.1 Study design

☐ A prospective confirmatory clinical trial of double-blinded (subjects-evaluator), multi-center, randomized and non-inferiority

☐ Experimental product (test group) : MegaShield

☐ Comparator (control group) : Guardix-SG

This is a prospective confirmatory clinical trial of double-blinded (subjects-evaluator), multi-center, randomized and non-inferiority which is performed by setting the test group and the control group. Subject identification codes are assigned only to subjects who are judged to meet the inclusion/exclusion criteria among those who are in need of total thyroidectomy. In addition, subjects are given a randomization code (3 digits) in order according to the randomization table and assigned to the corresponding application group. The randomization code and subject identification code will be used as the subject number during the clinical trial.

(For details, see 11.2.4 Assignment of subject number and 11.3.1 Randomization.)

This clinical trial is a double-blind trial, and both subjects and evaluator should be blinded. The evaluator is an independent evaluator and does not participate in surgery, so it is not possible for him/her to know which investigational product was applied to the subject. And since he/she contacts the subject only during evaluation, blinding will be maintained. Since the subject is applied with the assigned investigational product while under general anesthesia during surgery, he/she cannot know which investigational product has been applied, and does not know even after the surgery. Thus, subjects and the independent evaluator are blinded during the clinical trial.

### 10.2 Experimental product (test group)

- ☐ Classification : Dressing, adhesion barrier(B07070.14, Class 3)
- ☐ Model name : 3 items including AAB010 (MegaShield)
- ☐ Manufacturer : L&C Bio Inc.
- ☐ Raw material : poloxamer 407 + Acellular Dermal Matrix + HA (Sodium Hyaluronate) +1,4- BDDE (Butanediol diglycidyl ether)
- ☐ Shape, structure and dimensions : A transparent or milky gel with a mixture of human-derived acellular dermal matrix powder and cross-linked hyaluronic acid in a syringe filling with thermo-sensitive polymer. 1 each 2ml/syringe and 3ml/syringe
- ☐ Purpose of use: Prevent (or reduce) adhesion at thyroidectomy
- ☐ How to use:

A. Preparation before use

- 1) Check the packaging condition for any abnormality, and check whether the sterilization label is attached and sterilization status.
- 2) Check the expiration date.
- 3) The operator should fully understand how to handle and operate it before using it.
- 4) Use it after familiarizing with the instructions.
- 5) End-use physicians and institutions should store the product in an appropriate storage environment before use.

B. How to operate and use

The aseptic technique should be maintained to minimize the risk of postoperative complications.

- 1) Remove the cleaning solution used during the surgery from the body and check if the bleeding on the wound surface has stopped.
- 2) Remove the double packaging and hand the inner package over to the surgical participant wearing sterile clothing, taking care not to contaminate it.
- 3) Check if the inner package is not damaged.
- 4) Remove the inner package, take out the syringe, remove the cap of the syringe, and then mount the catheter.
- 5) Slowly push the plunger to inject the contents so that it can be fully applied to the surgical area.
- 6) After using once, do not reuse the remaining contents.

C. How to store and control after use

This product is disposable, so dispose of it according to the appropriate procedures after use.

D. Remove or disassemble after application :

It is known that poloxamer, the raw material of MegaShield, is metabolized in the liver and excreted through the kidneys [18,19,20]. In addition, the particulate acellular dermal matrix can be biodegraded by collagenase (Matrix Metalloproteinase, MMP-1), a protease, and hyaluronic acid is degraded by hyaluronidase in the body [21]. Most of decomposed products are known to

be released as respiratory gas through the lungs or to be emitted to the outside of the body through the liver or kidneys [22].

[figure not shown]

[MegaShield 2ml/syringe]

[figure not shown]

[MegaShield 3ml/syringe]

### 10.3 Comparator (control group)

- ☐ Item name : Dressing, adhesion barrier(B07070.14, Class 3)
- ☐ Model name : Guardix-SGn-060 (Guardix-SG)
- ☐ Manufacturer : Genewel Co., Ltd.
- ☐ Raw material : poloxamer + sodium alginate
- ☐ Shape, structure and dimensions : Translucent white liquid filled in a syringe, 1 each 6ml /syringe
- ☐ Purpose of use: Prevent (or reduce) adhesion at thyroidectomy
- ☐ How to use:

#### A. Preparation before use

- 1) Do not open the package until immediately before use.
- 2) The package must be opened in a sterilized place when using the product.

#### B. How to operate and use

- 1) Remove the cleaning solution used during surgery by sucking it with an aspirator.
  - 2) Check if the bleeding on the wound surface has sufficiently stopped during surgery.
  - 3) Unpack the product in a sterilized place, remove the cap of the syringe, and then screw the catheter tube.
  - 4) Sufficiently inject the Guardix-SG solution to ensure that the solution is completely applied to the spinal or thyroid surgery area.
- ※ To apply the same amount as the experimental product applied to the test group, use 5 ml based on the scale of the syringe and leave 1 ml as the remaining amount. The researcher should document that only 5 ml of the comparator was used, and the sponsor should check and file it. (To ensure accurate use of 5 ml, it is also possible to remove 1 ml of Guardix-SG before surgery and apply all the remaining 5 ml to the subject.)

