(3) Adverse events should be followed up until the symptoms disappear, and if it is difficult for a subject to visit, the follow-up should be performed by phone. (However, if a subject is diagnosed with hypothyroidism or hypoparathyroidism through thyroid function test after thyroidectomy, the resulting adverse events should be followed up until the last visit of the subject for the clinical trial.)

Receive informed consent to participate in the clinical trial from patients who are judged to be in need of total thyroidectomy. After checking the results of hematological test, serum biochemical test and urinalysis, and the inclusion/exclusion criteria, assign a subject identification code only to subjects judged to meet the criteria. In addition, give subjects the randomization number (3 digits) in order according to the randomization table and assign the subjects to the appropriate application group. The randomization code and the subject identification code will be used as the subject number during the clinical trial. The target patient shall have total thyroidectomy and then be subject to the assigned investigational product. When applying the investigational product, apply 5 ml of MegaShield and 5 ml of Guardix-SG for the test group and the control group, respectively, on the thyroidectomy site and the surface of strap muscles. Visit the 1st and 6th weeks after surgery to evaluate the efficacy and safety.

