### 14.3 Analysis set

In the efficacy analysis of this clinical trial, the main analysis is the mITT set, and the PP set is additionally analyzed. The analysis for the safety is ITT set.

- ITT Set: An analysis set targeting for subjects who have received treatment at least once with an investigational product, among all subjects enrolled in this clinical trial
- Modified ITT Set: An analysis targeting for subjects who have received treatment at least once with an investigational product and participated in the primary efficacy endpoint evaluation, among all subjects enrolled in this clinical trial
- PP set: An analysis targeting for subjects who completed the study in accordance with this protocol without any significant violation of the protocol among ITT set

The exclusion criteria from the PP set because it is considered a serious violation of the protocol is as follows.

- 1) Violation of inclusion/exclusion criteria
- 2) Administration of drugs prohibited from concurrent use during the clinical trial
- 3) Other cases where it can be considered a serious violation of the protocol

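### The protocol does not withhold the allocation from the operating team until resection is finished, and a randomised patient who is not treated belongs to no analysis set

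*Protocol*

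**What the plan says.** **Who is blinded.** Protocol 10.1 states: "This clinical trial is a double-blind trial, and both subjects and evaluator should be blinded". It explains the evaluator's blinding by absence from the operation: the evaluator "does not participate in surgery, so it is not possible for him/her to know which investigational product was applied to the subject". The operating team is not listed as blinded.

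**When the arm is assigned.** In 10.4, the randomisation number and group assignment follow the screening checks. Surgery comes next: "The target patient shall have total thyroidectomy and then be subject to the assigned investigational product". The protocol summary gives the same order.

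**What the products look like.** The test product comes as "1 each 2ml/syringe and 3ml/syringe" (10.2). The comparator is a single 6 ml syringe of translucent white liquid (10.3).

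**When the comparator is prepared.** Part A of the instructions in 10.3 says: "Do not open the package until immediately before use". In part B, the bleeding check is step 2 and unpacking is step 3. The note below those steps then adds that "it is also possible to remove 1 ml of Guardix-SG before surgery and apply all the remaining 5 ml to the subject".

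**Who is analysed.** Section 14.3 defines ITT as "subjects who have received treatment at least once with an investigational product, among all subjects enrolled in this clinical trial". The mITT set, which is the main efficacy set, also requires the primary endpoint evaluation. The PP set is drawn from ITT. ITT itself is used only for safety. Section 13.4 says that a dropped-out subject is included in the statistics for both safety and efficacy, and 13.2 says the same of discontinued subjects.

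**The concern.** Two gaps meet at the same point in the trial. First, nothing in the protocol withholds the arm from the surgeons between assignment and the end of the resection. Blinding the evaluator six weeks later cannot undo a difference in dissection, haemostasis or willingness to apply the product that arose because the surgeon knew the arm. Second, a patient who is randomised but not treated, for example because the operation changed or a product-specific contraindication emerged, is in none of the three sets. If the person who decides on application knows the arm, such losses need not be balanced between arms.

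In a non-inferiority comparison of mean scores with a margin of 0.1 on an integer scale from 0 to 3, a few unbalanced losses can matter. Losses of worse-scoring patients from the test arm favour a finding of non-inferiority.

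**Working it through.** **1. Can the arm be known before the resection is complete?**

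- Assignment comes before surgery (10.4).
- Section 11.3.1 limits access to the randomisation table and code to people outside the institution. That protects the list. It does not mask two visibly different products once the assigned one is brought out.
- The default steps for both products put opening after the bleeding check: in 10.2 B, step 1 then step 2; in 10.3 B, step 2 then step 3. If these steps are followed, the product is seen only after resection.
- The optional note in 10.3 permits a comparator-only step before surgery. It conflicts with 10.3 A and with the step order in 10.3 B. It does not say who removes the 1 ml.

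So knowledge of the arm during dissection is permitted but not certain.

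**2. Where does a randomised but untreated patient go?**

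| Set (14.3) | Requires treatment? | Holds an untreated patient? |
|---|---|---|
| ITT (safety) | yes | no |
| mITT (main efficacy) | yes, plus primary evaluation | no |
| PP (additional efficacy) | yes, as a subset of ITT | no |

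Sections 13.2 and 13.4 say discontinued and dropped-out subjects are counted, but no defined set can hold an untreated one. The word *enrolled* does not settle it either. Section 11.1 lists enrolment at Visit 2 after surgery and application, the schedule table lists it above them, and 10.4 assigns the group before surgery.

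**3. The plan's own figures.** Inputs from 8.4: margin 0.1, SD 0.2, one-sided 0.025, power 80%.

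n = 2 × (1.96 + 0.84)² × 0.2² / 0.1² = 62.72, which rounds up to 63 per group. The protocol prints 62.8, which gives the same 63. Then 63 / 0.9 = 70. The sample size is not in dispute.

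**4. Sensitivity, on assumed inputs.** The protocol gives neither the number of selective losses (k) nor how much worse those patients would have scored (d). Both are assumptions.

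- Simple shift: three patients one grade below the remaining 67 give 3 × 1 / 70 = 0.043, and 0.043 / 0.1 = 43% of the margin. Measured against the mean of the full arm instead, it is 3 / 67 = 0.045.
- Error rate: take a true difference of −0.1, so that non-inferiority is false, 70 randomised per arm, and k patients lost from the test arm who would have scored d below that arm's mean. Keep the SD at 0.2. Then shift = k·d / (70 − k), SE = 0.2 × √(1/70 + 1/(70 − k)), and the one-sided error is 1 − Φ(1.96 − shift/SE).
- Example with k = 3 and d = 1: shift = 0.0448, SE = 0.0342, ratio = 1.31, error = 1 − Φ(0.65) = 0.258.

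| k lost from test arm | d = 0.2 | d = 0.4 | d = 1.0 |
|---|---|---|---|
| 1 | 0.030 | 0.037 | 0.063 |
| 3 | 0.045 | 0.076 | 0.258 |

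The nominal value is 0.025. The table shows how sensitive the decision rule would be to such losses. It does not estimate a bias in this trial.

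**The case against.** The strongest reply is that the protocol's ordinary steps already place unpacking after haemostasis. Visible syringe differences then tell the surgeon nothing during dissection, and the case rests on one optional remark, for one product, that names no person. Someone who is not operating could remove the 1 ml. This stands. A reader might infer that the surgeons do know the arm before they operate. The documents do not support that; they show only that nothing prevents it and that the instructions conflict.

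A second reply is that the illustration is not drawn from the trial. One grade is five times the planned SD. At the comparator mean of 2.93 cited in 8.4, if every abnormal score were 2, about 0.07 × 70 = 4.9 patients, or five per arm, would score below 3. If the test arm were truly 0.1 lower, at 2.83, it would be about 0.17 × 70 = 11.9, or twelve. Picking out three of those in the operating room, six weeks before the esophagography, asks a great deal. This also stands. A reader might take 0.258 as the trial's real error rate, and nothing in the protocol supports that.

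A third reply is that redefining ITT changes nothing in the main analysis, because efficacy is judged on mITT and 14.4 plans no imputation for the primary endpoint. This is correct, and the fix has to go further than the label.

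A fourth reply is that drop-out reasons are already recorded (13.4), a screening and enrolment log is kept (11.2.4), and listings of untreated patients can be left to the statistical analysis plan. This stands only in part. The sets are fixed in 14.3 in terms that 13.4 contradicts, and the timing of disclosure is trial conduct, which an analysis plan cannot repair.

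**Conclusion.** The point holds as an avoidable weakness, not as a demonstrated bias. Three things follow directly from the text:

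- The operating team is not blinded, and no disclosure time is fixed between assignment and the end of resection.
- The preparation note in 10.3 conflicts with the opening instruction and the step order in the same section.
- A randomised but untreated patient is in no analysis set, against 13.4.

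Whether any team would learn the arm early, and whether any patient would be left untreated because of it, cannot be read from the protocol. The size of any bias cannot be derived either. The 0.043 shift and the error rates shown rest on assumed counts, assumed score deficits, an SD held at 0.2 and a normal approximation. The change is worth making because it is cheap and closes a route to both performance and selection bias.

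**What to change.** 1. In 10.4 and 11.3.1, state that the allocation is disclosed to the operating team only once thyroidectomy is complete and haemostasis confirmed, or randomise at that point.
2. Reconcile the optional preparation note in 10.3 with the package-opening instruction, the step order and this timing. State at which point in Visit 2 a subject counts as enrolled.
3. Reconcile 13.2 and 13.4 with 14.3. Define ITT as all randomised subjects, analysed as assigned, and keep a separately named treated set for safety.
4. Report by arm, with reasons, every subject randomised but not treated and every subject treated but not evaluated at 6 weeks.
5. Add a sensitivity analysis of the primary endpoint in the all-randomised set, with its handling of missing scores stated, since renaming ITT leaves the mITT result as it is.

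The cost is amendment wording, sealed allocations opened in the operating room, a short wait while the product is prepared, and one further analysis. The planned 140 subjects need not change.

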#### C. How to store and control after use

- 1) As the product is disposable, the remaining solution should be discarded after administration

and should not be reused.

D. Remove or disassemble after application : Guardix-SG contains, poloxamer, a raw material with thermo-sensitivity. This substance is metabolized in the liver and excreted through the kidneys, like the experimental product, MegaShield [18,19,20]. And, it is known that calcium ions in alginate gradually spread out of the gel, and alginate is slowly decomposed and discharged through urine [23].

## 10.4 Study procedure

### 【Schedule of Clinical Study】

| Item                                         | Screening | Application and Evaluation |         |          |
|----------------------------------------------|-----------|----------------------------|---------|----------|
| Visit                                        | Visit 1   | Visit 2                    | Visit 3 | Visit 4  |
| Day                                          | -30~0     | Day 0                      | Day 7±3 | Day 42±7 |
| Written consent                              | ●         |                            |         |          |
| Inclusion/exclusion criteria                 | ●         |                            |         |          |
| Demographic survey/physical examination      | ●         |                            |         |          |
| Vital signs test                             | ●         |                            |         | ●        |
| Medical/administering history  | ●         |                            |         |          |
| Subjects enrollment                          |           | ●                          |         |          |
| Surgery and applying investigational product |           | ●                          |         |          |
| Esophagography                               |           |                            |         | ●        |
| Evaluating adhesion scores                   | ●         |                            | ●       | ●        |
| Urine β-HCG testing (for fertile women)      | ●         |                            |         | ●        |
| Hematological test                           | ●         |                            | ●       | ●        |
| Serum biochemical test                       | ●         |                            | ●       | ●        |
| Urinalysis                                   | ●         |                            | ●       | ●        |
| Collecting concomitant drug    | ●         | ●                          | ●       | ●        |
| Collecting adverse event       |           | ● (After surgery)          | ●       | ●        |

(1) Collect medical history within 5 years before participating in the clinical trial.

(2) Collect information on drugs that have been administered within 4 weeks of the screening visit or are currently being administered.

(3) Adverse events should be followed up until the symptoms disappear, and if it is difficult for a subject to visit, the follow-up should be performed by phone. (However, if a subject is diagnosed with hypothyroidism or hypoparathyroidism through thyroid function test after thyroidectomy, the resulting adverse events should be followed up until the last visit of the subject for the clinical trial.)

Receive informed consent to participate in the clinical trial from patients who are judged to be in need of total thyroidectomy. After checking the results of hematological test, serum biochemical test and urinalysis, and the inclusion/exclusion criteria, assign a subject identification code only to subjects judged to meet the criteria. In addition, give subjects the randomization number (3 digits) in order according to the randomization table and assign the subjects to the appropriate application group. The randomization code and the subject identification code will be used as the subject number during the clinical trial. The target patient shall have total thyroidectomy and then be subject to the assigned investigational product. When applying the investigational product, apply 5 ml of MegaShield and 5 ml of Guardix-SG for the test group and the control group, respectively, on the thyroidectomy site and the surface of strap muscles. Visit the 1st and 6th weeks after surgery to evaluate the efficacy and safety.

